# A Multicomponent Intervention to Reduce Screen Time Among Children Aged 2-5 Years in Chandigarh, North India: Protocol for a Randomized Controlled Trial

**DOI:** 10.2196/24106

**Published:** 2021-02-11

**Keywords:** multimedia, digital-media, preschooler, sedentary behaviors, toddler, sedentary, screen, children, youth

## Abstract

**Background:**

Excessive digital screen exposure (≥1 hour per day) is associated with limited growth and development in children.

**Objective:**

This study aims to develop and assess a multicomponent intervention program's effectiveness in reducing excessive screen time among children aged 2-5 years.

**Methods:**

A theory-based multicomponent intervention known as Program to Lower Unwanted Media Screens (PLUMS) at the household level has been developed. It is based on the social cognitive theory for children and self-determination theory for caregivers. After pretesting, a randomized control trial will be conducted to assess this intervention's effectiveness among healthy children aged 2-5 (±3 months) years and their primary caregivers who have at least one digital media gadget at home in zone three of Chandigarh (population of 2,730,035). A sample size of 428 children is estimated per arm. PLUMS includes disseminating specific information, education, communication in the form of videos and posters to the primary caregivers, and conducting motivational interviewing as and when needed. Children will be provided suggestions for playful activities as alternatives to digital media gadgets. The primary outcome is the mean change in the duration of screen time, and secondary outcomes are sleep duration and patterns, emotional-behavioral problems, and level of physical activity of the children. Per-protocol and intention-to-treat analyses will be conducted using SPSS for Macintosh, Version 25.0.

**Results:**

The intervention package will be disseminated once a week for 8 weeks to the participants via the caregivers' preferred means of communication. The endline assessment will be done immediately postintervention and after the 6 months of follow-up. The 
Institute's ethics committee, Postgraduate Institute of Medical Education and Research, Chandigarh, India, has approved this study (INT/IEC/2019/000711). The Indian Council of Medical Research, New Delhi (3/1/3/Next-100/JRF-2015/HRD), and PGIMER, Chandigarh (71/2-Edu-16/92, Dated 08/01/2018) funded this study.

**Conclusions:**

PLUMS might be effective in reducing excessive screen time among children aged 2-5 years in a North Indian Union Territory.

**Trial Registration:**

Clinical Trial Registry India CTRI/2017/09/009761; https://tinyurl.com/53q6dpjs

**International Registered Report Identifier (IRRID):**

DERR1-10.2196/24106

## Introduction

### Background

The overall impact of sedentary behaviors on health across the lifespan has gathered widespread recognition, as it plays a significant role in most noncommunicable diseases (NCDs) [1]. The Sustainable Development Goals 2030 [2] envisions reducing premature mortality from NCDs by one-third via the prevention, treatment, and promotion of mental health and well-being. Around 34% to 94% of children aged 2 to 5 years remain sedentary during the day [3]. The prevalence of television (TV) viewing for more than 2 hours per day was reportedly 83% in the United States [4] and up to 82% in Canada [5] in children less than 5 years old and 78% in Australia [6] among children aged 3 to 5 years. A Thai study reported that children aged 1 year viewed TV for 1.23 (SD 1.42) hours per day, which increased to 1.69 (SD 1.56) hours per day when they turned 2 years old [7].

Early childhood is a crucial period that is marked by rapid growth and development [8]. Therefore, it is essential to correct an excessively sedentary lifestyle at an early age. These sedentary pursuits may have specific health consequences during this period and later in life [9]. The health effects of excessive screen time (ST) include behavioral problems; poor language, cognitive development, skills, memory, and executive function; lower social competence; sleep disturbances; depression; and low self-esteem [10-17]. In light of this, the present randomized controlled trial was planned with an assumption that ST might be causally associated with emotional behaviors, sleep behaviors, and children’s level of physical activity. ST of more than 1 hour per day among children aged 2-5 years is deemed excessive as per the American Academy of Pediatrics [18]. Similar guidelines are available in many developed countries (Australia [19], New Zealand [20], France [21], Italy [22], Canada [23], and World Health Organization [24]) for children aged 2-5 years.

### Need for the Trial

A recent review [25] of intervention studies to reduce ST conducted in the last decade (2008-2018) has shown that all the studies (n=16) were conducted in developed countries. Behavior change theories were incorporated in most of the interventions. Educational material was shared with parents with or without their children. Nearly all the significant studies incorporated a postintervention follow-up. Published literature on ST reduction in low- and middle-income countries among young children is scarce [26,27]. Also, there is minimal evidence on the burden, impact, and effectiveness of interventions to reduce ST in Indian settings. Although some of the studies conducted in India have measured change in ST in young children, it was observed only as a secondary outcome [28]. As the number of TV users in India is almost equal to its population [27], designing an intervention to reduce ST among young children becomes more important. Given the Covid-19 pandemic situation, most children’s digital-screen exposure occurs at home as families are stuck at home with these media gadgets. Parents are an essential liaison of change between the child and health care worker [29]. Therefore, there is an urgent need to devise interventions for those of a younger age in the home environment to prevent adverse health consequences later in life.

### Study Objectives

Given this background, the current study aims to develop a Program to Lower Unwanted Media Screens (PLUMS) to reduce ST among children aged 2-5 years and assess the effectiveness of PLUMS on reducing ST among children in Chandigarh, Union Territory, North India. Effectiveness of the intervention will be determined using the percentage risk reduction of mean ST in the intervention group compared to the control group. As excessive ST is a much less emphasized epidemic, this study's results might focus policy makers on this issue and help them formulate guidelines regarding ST use among young children in India and other low- and middle-income countries.

## Methods

The intervention study will be conducted in 2 phases, including the preintervention phase used to develop the intervention and intervention phase, as described in the following sections.

### Phase I. Preintervention Phase

The multidimensional intervention package was designed in 3 stages, including literature review, formative research, and pretesting. All 3 stages were completed. The brief methodology and results of each stage are described in the following sections.

#### Stage I: Review of Literature

In the first stage, the draft PLUMS, including parent and child modules, was prepared after reviewing the existing literature from 2008-2018. Effective community-based interventions to reduce ST in children and the most commonly used theories or models to design the intervention program were identified [25,30]. The following 3 theoretical models were used: social cognitive theory, self-determination theory, and transtheoretical model of behavior change. Social cognitive theory and self-determination theory were used to develop the intervention, and the transtheoretical model of behavior change was used to understand the stage of behavior change of the caregivers, so that the intervention could be customized accordingly. These theoretical models are described in the following paragraphs.

Social cognitive theory was used to modify preschoolers’ cognitive development by developing targeted strategies to modify the behaviors of the caregivers and children regarding ST or the home media environment. Bandura’s social cognitive theory explains how learning occurs in a social context with a reciprocal and dynamic interaction of the person (here child or caregiver), behavior, and environment. This theory supports a causation model that involves triadic reciprocal determinism between behavioral (expectations, goals, and self-perceptions), personal (cognition, outcome expectation, and efficacy expectation), and environmental factors (reinforcement and observational learning). These factors influence each other bidirectionally (Multimedia Appendix 1). When designing the intervention, we used this theory’s framework of modeling (by the caregivers and health care worker), production (alternatives to ST, such as activities given to children or suggested by them), retention (repeated positive feedback provided by a health care worker), and reinforcement (rewards for encouraging positive behavioral outcomes offered by the health care worker) in observational learning, which is pivotal due to the limited cognitive development of preschoolers [18].

Self-determination theory was used to design the strategies to keep the caregivers motivated to limit the ST among the children and modify the home media environment. Self-determination theory [31] targets 3 primary needs: competence, autonomy, and internalization of the learned concepts leading to desired outcomes. This theory postulates that individuals are better motivated if they satisfy these 3 psychological needs, in turn, leading to positive health outcomes. High-quality learning and favorable outcomes have been observed with the combination of self-determination theory and motivational interviewing [32]. The 4 major motivational interviewing components are empathy, developing discrepancy, “rolling with resistance,” and supporting self-efficacy [33]. So, motivational interviewing, along with self-determination theory [34], will be used with the caregivers. Theory-based motivational interviewing will herald the researcher to instruct the caregivers (Multimedia Appendix 2). These motivated and self-determined caregivers will then role-model learned behaviors at home to realize the same in their children and subsequently change the home environment [31].

Last, the transtheoretical model of behavior change by Prochaska et al [33] will be used to modify the caregivers’ behaviors. The stage of change will be identified for each caregiver as per the transtheoretical model (Multimedia Appendix 3). The caregivers will be educated and guided towards the desired behavior, eventually preventing relapse.

#### Stage II: Formative Research

In the second stage, the children’s primary caregivers and trained clinicians suggested workable alternatives to ST for children as a result of the formative research. The ideas gathered were refined by an expert panel.

A qualitative study was conducted among parents of children aged 2-5 years and service providers working in a tertiary care hospital in Chandigarh, India. In-depth interviews were conducted (30-40 minutes) with caregivers (n=20) attending the outpatient department. Two focus group discussions were conducted (40-60 minutes) with the service providers (n=11) at a predecided venue and time. The interviews were conducted in the participant’s preferred language until data saturation using pretested guides (Multimedia Appendix 4). These interviews were audio-recorded with prior informed consent. Subsequently, thematic analysis was done on the transcribed and translated English versions.

To review and modify the activities and methods proposed by caregivers and clinicians, a consultation meeting with 3 experts (professor-level) from psychiatry, child psychology, and public health was conducted. To decelerate excessive and unregulated ST, the clinicians proposed to increase the quality of family time at home with structured parenting approaches. Caregivers should presume responsibility and effectively use leisure time for children and themselves with health care providers’ help when necessary.

The qualitative data obtained through formative research were transcribed and translated into the English language. Thematic analysis of the data was done manually based on grounded theory. Two authors coded the data independently. Both deductive and inductive logic was applied to reason the acceptability and experience of the participants.

The background information of the participants of the in-depth interview and focus group discussions is given in Supplementary Table 1 in Multimedia Appendix 5.

Among the 20 participants in the in-depth interviews, 14 were mothers, and 6 were fathers. The caregivers had a mean age of 34.2 years. Half (10/20, 50%) of the caregivers were educated until the post-graduate level, 50% (10/20) were working, and 40% (8/20) were public health experts. Most (15/20, 75%) of the mothers were the primary caregivers. They were directly involved in their child's behavior modification and introduced media gadgets to them. Digital media exposure usually occurred at home under adult supervision, and aversive measures were frequently used to regulate media gadgets. Most of the caregivers reported negative consequences of excessive ST on their child’s health like a change in sleep patterns, learning bad language, impaired emotional behavior, increase in sedentary behaviors, and deterioration in concentration; however, a few perceived a gain in knowledge and development of skills.

In the focus group discussions, the service providers (n=11) had a mean age of 29 years. They were mostly unmarried (9/11, 82%), female (7/11, 64%), and working as junior residents (6/11, 55%). Of the resident doctors, 7 were from the Department of Pediatrics, and 4 were from psychiatry. The clinicians had learned about managing such cases from research articles, methods taught by their seniors, and practical things that worked for their children. Also, they had adapted themselves to the guidelines from developed countries as none exist in India.

Regarding the intervention for children to reduce ST, they reported that at home, adults should instill healthy habits, develop hobbies, and communicate ill effects of excessive usage to their children using role modeling. At the school level or hospital level, a designated person should advise in a stepwise fashion using face-to-face communications with consistent modes of communication preferred by the participant. The intervention package was adapted as per the results of the qualitative study.

#### Stage III: Intervention: Program to Lower Unwanted Media Screens (PLUMS)

Two modules, one for the caregivers or parents and another for the children, were developed as part of the PLUMS intervention. The strategies were incorporated separately for caregivers and children. These modules have theme-based activities for the children and videos for the parents or caregivers to engage the children in media screen–free activities. PLUMS will be implemented for 8 weeks (2 months) and will consist of 8 themes. Details of these modules are provided in Supplementary Table 2 in Multimedia Appendix 5.

In the caregivers’ module, online videos will be disseminated weekly for 8 weeks via the parent’s preferred mode of communication. We developed the videos in Hindi and the English language. We developed 1 introductory video and 7 small video sessions based upon the weekly theme. Caregivers can go through the session in their own time as per their convenience, except for the introductory video. The introductory video is planned to be watched with the lead author for a better understanding of the caregivers. The introductory session will last 15-20 minutes, and the 7 weekly videos are 5 minutes long. These online video sessions’ primary objective is to help the parents change the home media environment, provide alternatives to ST, provide tips and cues for parenting skills, and engage the child in media-free activities of their choice. These videos will also provide 10 alternative activities per week for children. The caregivers will be encouraged to reward the children for abiding by the rules and accomplishing goals [35].

The child module’s lesson plans were drawn from educational disciplines like skill building, motor coordination, learning, goal setting, music, dance, arts, and crafts. This module contains activities for the child that need the caregiver’s supervision. To capture the child’s interest and channel their energy, specific activities have been selected. This module emphasizes observational learning and increasing the attention span of the child [36]. The curriculum will also allow children to repetitively and effectively learn the desired behavior(s) to facilitate the production and retention processes [36]. We will be providing the following resources as an alternative to screen time for the children: a reading book called “Chika Chika Boom Boom”; pretested and self-developed comic book on the consequences of ST; and coloring book with crayons.

#### Stage IV: Pretesting the Intervention

In the third stage, the PLUMS intervention, with its parent and child modules, was pretested among 10 families to assess the feasibility, acceptability, and adherence to the intervention plan. After the pretesting, the videos’ language was further simplified to match the parents’ understanding. The introductory video’s duration was reduced from 18 minutes to 12 minutes, as suggested by the families. The videos were made attractive by adding animations, bright colors, background music, and live videos of children (regarding behaviors) recommended by the parents. Additional indoor alternatives to ST were included for the children, as parents could not take the child for outdoor play due to Covid-19 pandemic restrictions. The child module now has 10 activities to choose from instead of 1 per day, as was planned earlier. The children will also be given a coloring book with crayons. The intervention was acceptable and feasible, and the caregivers were ready to adhere to the proposed plan.

Finally, the modified intervention module will be used in the main intervention study.

### Phase II: Intervention Study

#### Study Setting

This study will be conducted in Chandigarh, a North Indian Union Territory. It has a population of about 1,055,450 as per the 2011 census [37]. It is divided into 4 zones. This study will be conducted in Zone three, a field practice area of the Department of Community Medicine and School of Public Health, Postgraduate Institute of Medical Education and Research, Chandigarh, India (Multimedia Appendix 6). It has a population of 250,000 as per the 2018-2019 annual health survey. There are approximately 8681 children aged 2-5 years in this area.

#### Study Design

The intervention study is a randomized controlled trial.

#### Study Population

The study population includes the families (N=8681) with children aged 2-5 years (±3 months). The primary caregiver was considered the person who spent most of the time with the child and was involved in the child’s decision making for various activities. Inclusion criteria are families who consent to be part of the study, are residents of the study area in Chandigarh for at least the past 6 months, and who intend to stay in Chandigarh through the intervention and follow-up period. Children previously diagnosed (as per medical records) with long-term or chronic illnesses will be excluded from the study.

#### Sample Size

The sample size for the individual level randomization was estimated using the following formula [38]: n_I_= (σ_1_^2^+σ_2_^2^) (Z_1-α/2_+ Z_1-β_)^2^/Δ^2^, where n = sample size, σ_1_ = standard deviation of the control group and assumed to be 2.09 [39], σ_2_ = standard deviation of the intervention group and assumed to be 1.46 [40], Δ = difference in group means of the average ST and assumed to be 0.54 [39], Z_1-α/2_ = two-sided Z value (Z = 1.96 for the 95% CI), and Z_1-β_ = power (80%). Hence, n_I_ was 170 participants per arm. Considering a 10% attrition rate due to loss to follow-up and 15% nonresponse or refusal rate, the sample size per arm was calculated as 214.

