#### Baseline Assessment

The baseline data were collected from December 2019 to March 2020. During the baseline assessment, the mean ST, prevalence of excessive ST and its correlates, mean duration of physical activity, emotional problems, and sleep disturbances in both the intervention and control arms were measured.

To assess mean ST, physical activity, and prevalence of excessive ST, a pretested, validated, semistructured, bilingual (English and Hindi languages) digital screen exposure questionnaire (DSEQ) was used (Multimedia Appendix 7). The DSEQ was developed in 5 phases. In phase 1, a draft questionnaire was developed by reviewing the literature on existing tools (n=2) from 2009 to 2017. In phase 2, 9 experts assessed the draft Hindi and English questionnaires’ face and content validity. Face-to-face interviews with primary caregivers (n=30) were conducted in a tertiary care hospital for acculturation. In phase 3, a pilot study was conducted among randomly selected families to evaluate the feasibility of the DSEQ in field settings. During phase 4, test-retest reliability was assessed among 30 primary caregivers selected randomly in another urban cluster. In phase 5, the internal consistency of the DSEQ was checked by conducting a cross-sectional study among 400 randomly selected, primary caregivers in Chandigarh, North India. The DSEQ has good internal consistency (Cronbach α=0.73-0.82) and inter-rater agreement (kappa 0.75, 95% CI 0.72-0.78).

The DSEQ was used to collect information from the primary caregivers of the children on (1) sociodemographic profile including family type and socioeconomic status (BG Prasad classification, 2016) [42], (2) digital screen exposure and home media environment, (3) level of physical activity of the child, (4) child’s media-related behaviors, and (5) parental perceptions and literacy regarding digital screen exposure. We recorded the duration and content of media watched by the child on a typical day. The objective criterion to measure ST was the number of hours the child watched a specific TV program. Cinema and movies were excluded from the ST measurement to calculate the actual average of ST for a regular day. Besides, cinema and movies are not watched daily and might falsely increase ST.

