We used the 5 progressive physical activity levels among preschoolers given in the Preschool Physical Activity Questionnaire (PrePAQ) to assess physical activity. The PrePAQ categorizes activity into stationery (no action), sedentary (limb or trunk movement), slow-paced (moving easily or slowly), medium-paced (moving at a moderate pace), and fast-paced (quick pace or hard effort) [43].

The standard Preschool Child Behavior Check List was used to assess the child’s emotional and behavioral development. It has been validated in an Indian setting and has the right internal consistency (Cronbach α=0.95) [44]. It consists of 100 items with a 3-step response scale (0, 1, and 2). These items are scored as being absent (score, 0), occasionally present (score, 1), and very often present (score, 2).

The sleep disturbances scale for children was used to measure the child’s sleep patterns. It is a 26-item Likert-type scale that measures specific sleep disorders along with overall sleep disturbances in children. It has been validated and has an internal consistency of 0.71-0.79, test-retest reliability of 0.71, and diagnostic accuracy of 0.91 [40].

The lead author visited the homes of the study families and conducted face-to-face interviews during the baseline assessment.

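### The intervention-arm SD of 1.46 is cited to the sleep-scale reference and paired, without a reason, with a control SD of 2.09 from another source, so the stated 80% power is unsupported as documented

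*Protocol article*

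**What the plan says.** The Sample Size section uses the two-mean formula that allows a separate SD for each arm. Its inputs are:

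- Control SD: "standard deviation of the control group and assumed to be 2.09 [39"].
- Intervention SD: "standard deviation of the intervention group and assumed to be 1.46 [40"].
- Difference: "difference in group means of the average ST and assumed to be 0.54 [39"].
- Two-sided 5% level, "two-sided Z value (Z = 1.96 for the 95% CI"), and 80% power.

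The result is that "n_I_ was 170 participants per arm", which is then raised for losses and refusals, as follows: "Considering a 10% attrition rate due to loss to follow-up and 15% nonresponse or refusal rate, the sample size per arm was calculated as 214".

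Reference 40 appears again in the Baseline Assessment section, where it supports the psychometric figures of the sleep disturbances scale for children: "internal consistency of 0.71-0.79, test-retest reliability of 0.71, and diagnostic accuracy of 0.91 [40"]. The article nowhere describes reference 40 as a study of screen time.

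Under Sampling Technique and Randomization, families come from one list and are then allocated at random to the two arms. The Results section reports 440 enrolled and a second measurement of screen time before the intervention is delivered.

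**The concern.** There are two separate difficulties.

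The first is the source. As printed, the SD for one arm of a screen-time comparison is credited to a reference that the article otherwise uses only for a sleep scale. A reader cannot tell where 1.46 comes from or whether it measures screen time.

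The second would remain even if the reference number were a slip. Randomised arms drawn from one population share the same SD in expectation, and can differ later only if the intervention changes the spread. The calculation assumes an intervention SD 30% smaller than the control SD and a variance 51% smaller. It does so by taking one SD from each of two sources and gives no argument for the reduction. A difference between sources is thus carried into the calculation as if it were an effect of treatment on spread.

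At stake is the 80% power claim. If the spread in the intervention arm is close to the control value, the power for a difference of 0.54 is lower than stated, and a non-significant result would be weaker evidence against the programme than the article implies. If the spread in both arms is close to 1.46, the power is higher than stated.

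**Working it through.** **Inputs from the Sample Size section:** SDs 2.09 and 1.46, difference 0.54, z = 1.96 for two-sided 5%, z = 0.8416 for 80% power. **From Results:** 440 enrolled, taken here as 220 per arm (an assumption); less the stated 10% attrition this is 220 × 0.9 = 198 per arm. The Abstract gives 428 per arm, which is 2 × 214; the working follows the Sample Size section, with which an enrolment of 440 agrees better.

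**Step 1. Reproduce the article's figure.**

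n = (σ₁² + σ₂²)(1.96 + 0.8416)²/Δ²

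= (4.3681 + 2.1316) × 7.849/0.2916 ≈ 175 per arm.

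The article prints 170. The gap of 5 is small; at 170 the article's own inputs give 78.9% power.

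**Step 2. Size of the assumed difference in spread.**

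1.46/2.09 = 0.70, so the SD is 30% smaller. 1.46²/2.09² = 2.1316/4.3681 = 0.49, so the variance is 51% smaller.

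**Step 3. Number needed with one SD in both arms.**

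- 2.09 in both: 2 × 4.3681 × 7.849/0.2916 = 235.2, so 236 per arm.
- 1.46 in both: 2 × 2.1316 × 7.849/0.2916 = 114.8, so 115 per arm.

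**Step 4. Power at fixed numbers analysed** (normal approximation, m per arm):

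Power = Φ(0.54/√((σ₁² + σ₂²)/m) − 1.96)

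| SDs (control/intervention) | m = 170 | m = 198 | m = 220 (no loss) |
|---|---|---|---|
| 2.09/1.46 (as printed) | 78.9% | 84.6% | 88.1% |
| 2.09/2.09 | 66.4% | 72.9% | 77.3% |
| 1.46/1.46 | 92.6% | 95.7% | 97.3% |
| 1.56/1.56 | 89.1% | 93.1% | 95.3% |

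The last row uses the SD that the Background gives for TV viewing at age 2 in a Thai study. It is for context only: that study covers TV in younger children, whereas this trial measures any gadget at ages 2 to 5.

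**Step 5. What 198 per arm can support.**

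Detectable difference at 80% power = 2.8016 × √((σ₁² + σ₂²)/198): 0.51 with 2.09/1.46, 0.59 with 2.09 in both, 0.41 with 1.46 in both.

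Largest common SD that still gives 80% power for 0.54: (0.54/2.8016)/√(2/198) = 0.1927/0.1005 ≈ 1.92.

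**Step 6. Scale of the outcome.**

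The formula compares group means, while the Outcomes section names mean change. With a common SD σ and baseline-endline correlation ρ, the SD of change is σ√(2(1 − ρ)). With σ = 2.09 and 198 per arm, this falls to 1.92 when ρ is about 0.58. For a baseline-adjusted comparison the residual SD is σ√(1 − ρ²), which falls to 1.92 when ρ is about 0.40. The article gives no ρ, so these are thresholds and not estimates.

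**The case against.** A reader might infer that reference 40 is a sleep study and that 1.46 is therefore not a screen-time SD. The article does not support that. The text reviewed has no reference list, so the number could be a slip in either section, or one study could report both measures. Reference numbers are used loosely elsewhere: 38 serves both the sample-size formula and studies of TV viewing, and 25 serves both the review of interventions and self-determination theory. The value is plausible for screen time, since the Background gives SDs of 1.42 and 1.56 hours per day for TV viewing. What remains is that the figure has no identifiable screen-time source as printed.

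A reader might also infer that the trial has only 66% power. That is the adverse end of a sensitivity range: it needs 2.09 in both arms and only 170 analysed per arm. With the enrolled number less 10%, the printed SDs give 84.6%, which is above the claim.

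Unequal SDs are not an error in themselves. Screen time cannot fall below zero, so spread may shrink as the mean falls. If SD is proportional to the mean (an assumption), a fall of 0.54 from a control mean of about 0.54/0.30 = 1.8 would give just the 30% reduction assumed. This is a fair argument, but the article does not make it, and the two SDs come from two sources and not from one such model.

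Finally, the SD of change may be smaller or larger than the cross-sectional SD, depending on the correlation. This stands, and it is why 66% or 73% should not simply replace 80%.

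**Conclusion.** The point holds as a matter of support and not of proven error. An input that sets the sample size has no screen-time source as documented, and its pairing with a larger control SD from another source is unexplained. The 80% claim therefore cannot be relied on as it stands.

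Using the two printed SDs singly and together, power runs from 66.4% to 92.6% at 170 per arm and from 72.9% to 95.7% at 198 per arm. Whether 80% is reached at 198 per arm turns on whether a common SD is at or below about 1.92, and the article offers nothing that settles this.

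These figures assume a normal approximation, a two-sided 5% level, a true difference of 0.54, an equal split of the 440 enrolled, 10% attrition and a comparison of group means. That 170 is printed where the inputs give 175 is a minor separate slip.

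**What to change.** In the Sample Size section:

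1. Correct the citation for 1.46, or name a screen-time source for it.
2. Replace the two-source pairing with one SD of average daily screen time for both arms, pooled over arms. The data exist or are planned: "The baseline data were collected from December 2019 to March 2020", and screen time is to be measured again before delivery. If a smaller spread under intervention is to be kept, state the reason.
3. Keep the 440 enrolled, and restate the power, or the difference detectable with 80% power, at that number less 10% attrition.
4. State that the figure is for a comparison of means, and that the SD of change depends on the baseline-endline correlation.
5. Until the pooled SD is available, show the power as a range over plausible SDs, for example the rows of the table above, and not as a single value.

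The cost is one recalculation and a revised paragraph. No further families or procedures are needed. The downside is that the stated power may become less favourable.
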